## Introduction

### Background and rationale {6a}

The treatment of rifampicin-resistant tuberculosis (RR-TB), TB resistant to the most powerful anti-TB drug, requires a more complex regimen than the treatment of rifampicin-susceptible TB and more frequently causes severe adverse drug reactions. Until 2016, 18–24 months long and poorly tolerated RR-TB treatment regimens were recommended [1]. These regimens were individualised, thus not standardised, and resulted in not much more than 60% treatment success [2].

In 2016, WHO recommended a standardised short treatment regimen (STR) for patients not yet exposed to second-line drugs and without resistance to the main components of this STR [3]. This STR had achieved a high cure rate (over 80%) among RR-TB patients in multiple programmatic settings [4–8]. However, this STR included a second-line injectable drug (SLID; amikacin, kanamycin or capreomycin), known for causing severe hearing loss as main adverse drug reaction [9]. A review showed that SLID had to be discontinued in about 10% of patients due to adverse events (AE) [10].

The increasing availability of novel drugs, such as bedaquiline (BDQ) and delamanid (DLM), and repurposed drug, such as linezolid (LZD) and clofazimine (CFZ), allow the designing of potent RR-TB treatment regimens solely relying on oral drugs. The 2019 WHO RR-TB treatment guidelines recommend replacing the STR’s SLID with bedaquiline [11]. WHO also recommends research on STR using both BDQ and LZD in patients who have not yet taken second-line drugs for more than one month and for whom fluoroquinolone resistance has been ruled out [12]. This WHO BDQ/LZD-containing all-oral STR resulted in 73% end-of-treatment success in South Africa [13, 14], considerably lower than 83% relapse-free cure obtained with the RR-TB treatment strategy used in Niger [8].

In Niger, patients are treated with a SLID-containing STR. The STR’s SLID is replaced by LZD in patients with contraindications for SLID, mainly ototoxicity. Audiometry is done at baseline and on a monthly basis during treatment. As any audiometry abnormality serves as an indication for switching to LZD, not a single RR-TB patient developed severe hearing loss since 2017 [15]. BDQ is safeguarded for the rare patients with treatment failure or relapse after a first STR, leaving not a single patient without a potentially successful retreatment option [8].

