### Criteria for discontinuing or modifying allocated interventions {11b}

A clinical committee may decide to modify the treatment regimen to start an individualised regimen in patients with specific problems. The most common situations for which the regimen may be discontinued include :Results of baseline DST may not be available before the start of treatment. If resistance to components of the treatment regimen is reported after the start of treatment it may be necessary to modify the treatment regimen taking into account DST results.Grade 3 or higher toxicity may lead to the temporary or permanent suspension of one or more drugs, which then may need to be replaced.Treatment failure (see the “Definition” section). In such patients, a new RR-TB treatment regimen is warranted. For the control arm, 4-6 Lzd-Hh-Bdq-Dlm-Cfz-Z/5 Bdq-Dlm-Cfz-Z will be used as re-treatment RR-TB regimen. For the experimental arm, the composition will be based on DST. The evaluation of re-treatment outcomes is not part of this study.

In patients with renal insufficiency the regimen is adapted as follows:If renal failure is present before the start of treatment, the SLID is replaced with LZD (similar approach as when audiometry abnormalities are present) and pyrazinamide is administered thrice weekly instead of daily.If during treatment with SLID the creatinine clearance is less than 90 ml/min, the SLID is prescribed twice or thrice weekly at 12–15 mg/kg; and ethambutol and pyrazinamide are given thrice weekly. If creatinine clearance is less than 60 ml/min the SLID will be replaced with LZD, while ethambutol and pyrazinamide are administered 3 times a week instead of daily.

Safety data collected during treatment with either the control or experimental regimen will be included in the safety analysis. Effectiveness data will be used from all patients enrolled on RR-TB treatment. However, if the regimen was changed during treatment to better fit the initial resistance pattern, such a patient will be excluded from the effectiveness analysis, as the patient had a contra-indication for the study regimen (see the exclusion criteria).

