### Relevant concomitant care permitted or prohibited during the trial {11d}

In RR-TB patients co-infected with HIV and on antiretroviral drugs we take into account the following measures:Tenofovir and SLID: strict monitoring of kidney function.Atazanavir and LZD: strict monitoring of the hemogram.Efavirenz (inducer of CYP3A4, thus decreases the concentration of BDQ) should not be used with BDQ.Protease inhibitors (inhibitors of CYP3A4, thus increase the concentration of BDQ) and BDQ can be used together with caution.Nevirapine and BDQ can be used together without problems

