## Statistical methods

### Statistical methods for primary and secondary outcomes {20a}

#### Primary analysis

The proportion of patients with grade 3–5 AE will be compared between the experimental treatment arm and the control arm using a chi-square test (or exact Fisher test). A Cox regression model will be developed to measure the association between enrolment in either the experimental or control arm and the incidence of a grade 3–5 AE. All patients who started treatment will be included. The start of follow-up time will be the date of start of treatment. The end of follow-up time will be the date an AE was graded as grade 3–5. In patients without AE, the date of the end of treatment will be used if they were cured or completed treatment, or the date of the last visit in case the patient was lost to follow-up before ending the treatment, or the date of death in case the patient died during treatment.

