#### Secondary analysis

By treatment arm, safety will be calculated as the proportion of all patients started on treatment and without any severe AE (safety endpoint). By treatment arm, treatment effectiveness will be calculated as the proportion of patients with a favourable outcome among all patients with either a favourable or unfavourable outcome. By treatment arm, adherence will be calculated as the proportion of patients who took at least 90% of the doses of RR-TB treatment. Cohorts will be compared using the chi-squared test. Bivariable and multivariable logistic regression models will be used to estimate the association between having an unfavourable treatment outcome and treatment arm (experimental vs control; the variable of interest), adjusted for potential confounding factors such as age, sex, HIV status, type of tuberculosis, bacillary load, extent of disease, body mass index (BMI) and initial resistance pattern. Factors associated (*p*-value <0.1) with having an unfavourable outcome will be included in the multivariable model, which then will be simplified by backwards elimination until all remaining factors have a *p*-value <0.05 (treatment arm, the variable of interest, will not be removed).

An additional Cox regression model will be developed to estimate the association between the variable “exposure to SLID vs LZD” and having a grade 3–5 AE probably or definitively related to either the SLID (ototoxicity) or LZD (haematological disorders, optic neuritis, neurological disorders). The variable “exposure to the injectable vs linezolid” will be treated as a time-dependent covariate, as described previously [15].

Analyses will be carried out with Stata software (version 16.1, College Station, TX).

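### The additional SLID-versus-LZD Cox model counts only ototoxicity as a SLID event, leaving out the renal toxicity that the protocol itself manages as a SLID harm

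*Protocol article*

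**What the plan says.** The Secondary analysis section of the protocol article adds a Cox model for SLID versus LZD exposure. The event is a grade 3–5 AE, probably or definitively "related to either the SLID (ototoxicity) or LZD (haematological disorders, optic neuritis, neurological disorders". Exposure "will be treated as a time-dependent covariate, as described previously [15", so its coding is left to a cited earlier study.

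Other sections link the SLID to the kidney:

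- **Criteria for discontinuing or modifying allocated interventions {11b}:** the rule beginning "If during treatment with SLID the creatinine clearance is less than 90 ml/min" changes how the SLID is given. Below 60 ml/min the SLID gives way to LZD.
- **Relevant concomitant care {11d}:** "Tenofovir and SLID: strict monitoring of kidney function".
- **Participant timeline {13}, Table 1 and its footnotes:** creatinine and potassium carry the mark for patients taking a SLID.

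On hearing, Background and rationale {6a} says: "As any audiometry abnormality serves as an indication for switching to LZD". It reports that "not a single RR-TB patient developed severe hearing loss since 2017".

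**The concern.** The parenthesis after the SLID names one toxicity and reads as the definition of what counts. A grade 3–5 renal or electrolyte event that the study physician judges definitely due to the SLID falls outside it. If that event also brings the patient under the clearance rule, the SLID is replaced with LZD and the patient goes on contributing LZD time, with no event recorded for the SLID.

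The one SLID toxicity that does count is also the one the strategy is built to stop early, so the countable SLID numerator may be very small.

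This is the only stated model that compares exposure to the two drugs rather than the two arms. The trial's hypothesis is that the all-oral regimen, with LZD for all, is less safe than the control strategy. An event definition that leaves out a recognised SLID harm leans the same way as that hypothesis.

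**Working it through.** **1. What the plan computes.** The SLID-versus-LZD model has no sample size or target ratio of its own, so there is no figure to reproduce for it. The trial's stated size concerns the primary comparison and can be checked. With HR 3.2, two-sided alpha 0.05 (sidedness is not stated), power 0.80 and 1:1 allocation, the Schoenfeld formula gives

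events = 4 × (1.960 + 0.842)² / (ln 3.2)² = 4 × 7.849 / 1.353 = 23.2.

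With a mean event share of (5% + 15%)/2 = 10%, N = 23.2 / 0.10 = 232, close to the stated 230. That calculation rests on any grade 3–5 AE, so the present point does not touch it.

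**2. Which events count.**

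| Toxicity | Treated in the protocol as a concern of | Counts in the SLID-versus-LZD model |
|---|---|---|
| Hearing | SLID (audiometry, switch rule) | Yes |
| Renal, potassium | SLID ({11b}, {11d}, Table 1) | No |
| Haematological, optic, neurological | LZD | Yes |

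The second row is the inconsistency.

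**3. Direction and illustrative size.** Let r be the share of severe SLID-related toxicity that is not ototoxicity and so is not counted. If the true rates of drug-related severe toxicity are equal, the observed LZD:SLID rate ratio is 1 / (1 − r):

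- r = 0: 1.00
- r = 10%: 1 / 0.90 = 1.11
- r = 25%: 1 / 0.75 = 1.33
- r = 50%: 1 / 0.50 = 2.00

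The values of r are assumptions; the documents give none. The r = 0 line shows that listing three classes for one drug and one for the other creates no bias by itself. Bias arises only from a real SLID toxicity that is left out.

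**4. What the earlier cohort can tell us.** Sample size {14} gives 6 of 153 patients (3.9%) with a grade 3–5 AE under the strategy, and 6 of 33 (18.2%) among those given LZD. If the 33 are part of the 153 and the six patients are the same, which the article does not state, then 153 − 33 = 120 other patients had 6 − 6 = 0 events. The exact two-sided 95% upper limit is 1 − 0.025^(1/120) = 3.0%. With a base this low, a few added or omitted SLID events would move the ratio a great deal, and with none it cannot be estimated.

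**The case against.** **The earlier cohort does not show a material omission.** The 6 of 153 covers grade 3–5 AEs of any type. If the 0 of 120 inference is right, it includes renal events, and adding them would have changed nothing in that subset. The clearance rule may also keep renal toxicity from reaching grade 3. This stands: the cohort gives no evidence that the bias is large, although an upper limit of 3.0% does not exclude such events.

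**The listed classes are each drug's characteristic toxicities.** This is legitimate, and the article calls hearing loss the SLID's main adverse reaction. A reader might infer that one class against three tilts the comparison by definition. It does not, as the r = 0 case shows.

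**Hearing loss after the switch.** A reader might also infer that SLID hearing loss that worsens after the mandated switch will be charged to LZD. That would follow if exposure were coded as the current drug and the event dated by the rule "The end of follow-up time will be the date an AE was graded as grade 3–5". But that dating rule is stated only for the primary Cox model, and the exposure coding sits in a cited study that is not shown. With no severe hearing loss reported since 2017, few or no such events are expected. What remains is that the article states no attribution rule.

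**Scope.** The model is described as additional and appears in neither the objectives nor the listed endpoints. Severe renal events do count in the primary comparison, the secondary safety proportion and the interim analyses. This stands and limits the finding.

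**Detection.** Creatinine and potassium tests are tied to SLID use, so adding laboratory events brings in detection that depends on exposure. This also stands, and is a cost of the fix.

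**Conclusion.** The point holds in a limited form. The stated event definition leaves out renal and electrolyte toxicity, which the protocol elsewhere treats as a SLID harm and, for the kidney, as a reason to move to LZD. Any such grade 3–5 event judged probably or definitely SLID-related would be missed, and the comparison would favour the SLID. This takes the parenthesis as exhaustive, which is its plain reading.

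The size cannot be computed from the documents. The ratios of 1.11 to 2.00 are illustrations under assumed shares, and the bias is nil if no such events occur. The documents do not support saying that the model is biased by construction or that late hearing loss will be misassigned. The consequence is confined to one additional secondary model; the primary analysis stands.

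**What to change.** - **Event definition:** count every grade 3–5 AE judged probably or definitely related to either the SLID or LZD, including renal and electrolyte events. The named toxicities can stay as examples.
- **Attribution after a switch:** assign hearing loss graded 3–5 after the switch to prior SLID exposure. Cause-specific models are an alternative: hearing and renal events by SLID exposure, and haematological, optic and neurological events by LZD exposure.
- **Sensitivity analysis:** report any grade 3–5 AE by exposure, without regard to causality.

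The cost is a change of wording and a little more analysis. AE type, grade and month are already recorded (Adverse event reporting and harms {22}), and causality is already assessed (Table 3). No treatment or monitoring rule changes. The report should acknowledge that laboratory monitoring differs by drug (creatinine and potassium for the SLID, blood count for LZD), so part of any difference may reflect detection.

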### Interim analyses {21b}

As soon as the safety data for 80 prospectively included patients are available, an intermediate analysis will be carried out to evaluate whether a significant association exists between the treatment arm (experimental vs control) and the occurrence of the safety endpoint (any grade 3–5 AE), using Cox regression, as described above for the primary analysis.

As the Niger approach to RR-TB treatment (SLID-containing STR with LZD replacing the SLID in case of audiometry abnormalities) was already successfully used and as data were collected rigorously, using the same procedures that will be applied in the trial, interim analyses will also include the retrospective cohort if the characteristics of the cohort are not significantly different from the prospective cohort with both treatment arms (the chi-square test will be used to compare HIV status, bacillary load, extent of TB disease and body mass index), and in case the proportion with a grade 3–5 adverse event is not significantly different between the retrospective cohort and those prospectively treated using the Niger RR-TB treatment strategy. To assess whether data from the retrospective cohort can be used, besides age and gender, characteristics known to predict safety (BMI, co-morbidities) and effectiveness (baseline bacillary load, baseline resistance profile) will be compared between the retrospective and prospective cohorts.

If the interim analysis shows a significant difference between the experimental arm and the control arm in terms of the primary endpoint before the total sample size is reached, study enrolment will be discontinued.

In case enrolment continued after the first interim analysis, and as soon as safety data are available for 160 patients enrolled in the trial, a second interim analysis will be conducted, using the same approach as used during the first interim analysis.

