### Sample size {14}

A total of 230 patients will be included prospectively to compare treatment arms (115 patients for each) in order to be able to identify a correlation between the treatment arms and the occurrence of any grade 3–5 AE, assuming that the “hazard ratio” for developing a grade 3-5 AE is 3.2 times higher among patients in the experimental treatment arm (WHO all-oral regimen) compared to the control arm (STR that contains either a SLID or LZD; 5% vs 15%; with power 0.8, alpha 0.05).

Justification of assumptions :Of the 153 patients already treated according to the Niger RR-TB treatment strategy, with LZD replacing the SLID in the STR in case of ototoxicity and with monthly audiometry, 6 (3.9%) had an AE of degree 3–5 [15]. For the calculation of the sample size, a “conservative” estimate of 5% was used.Of the 33 patients treated with linezolid instead of the SLID in case of ototoxicity, 6 (18.2%) had grade 3–5 AE [15]. A “conservative” estimate of 15% was used to calculate the sample size.

In addition to the prospective treatment arms, a retrospective cohort of 255 patients enrolled on treatment between 2017 and April 2021 will be used during an interim analysis (see interim analysis), if characteristics known to affect the treatment outcome of the retrospective cohort are not significantly different from the prospective arms, and in case the proportion with a grade 3-5 adverse event is not significantly different between the retrospective cohort and those prospectively treated using the Niger RR-TB treatment strategy (SLID-containing regimen, with LZD replacing the SLID in case of ototoxicity).

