### Dissemination plans {31a}

The results will be communicated through abstract presentations at scientific conferences and publications in peer-reviewed journals. The results of the intermediate analysis can be used for abstracts or manuscripts, prior to the publication of the results of the primary analysis.

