Second, we will conduct interim analyses to stop enrolment early in case the primary safety endpoint would be significantly more frequent in one of both arms. For the interim analysis, we will also consider including data from a retrospective cohort of patients treated in precisely the same way as in the control arm, in terms of treatment and monitoring procedures, including consent procedures and prospective collection of safety and treatment response data. We will verify whether the characteristics of the retrospective cohort are significantly different from those of the RCT cohort and whether the proportion with a grade 3–5 adverse event is significantly different between the retrospective cohort and those prospectively treated using the Niger RR-TB treatment strategy (SLID-containing regimen, with LZD replacing the SLID in case of ototoxicity). If not different, data from the retrospective cohort will be used. As such we aim to avoid a too long enrolment period and important delays between this study and informing national and international treatment guidelines. A previous analysis showed a higher rate of grade 3-5 adverse events in a small observational cohort of patients treated with a LZD-containing STR compared to the SLID-containing STR. With our trial, we therefore hypothesise that the risk of severe adverse events is higher among patients treated with the newly recommended WHO all-oral regimen, with LZD for all, compared to the control arm, with a STR that contains either SLID or LZD. If indeed, the new WHO all-oral regimen shows to cause more adverse drug reactions, it would ethically not be justified to expose more patients than needed to this regimen, especially considering the exceptionally good results obtained with the control arm in our setting.

The findings of our trial will immediately inform the implementation of RR-TB treatment by the Niger NTP. All RR-TB sites are involved, thus findings are generalisable to the reality of Niger. The NTP director is involved as a co-investigator and thus can guide the implementation of recommendations informed by our findings. Our findings will also inform the international debate on the balance between striving towards a RR-TB treatment regimen that is both safe and effective.

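### Enrolment stops on an unadjusted significant difference at 80 and 160 patients; if a crossing counts as the trial's conclusion, the overall type I error is about 10.6%, not 5%

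*Protocol article*

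**What the plan says.** **Sample size {14}.** "A total of 230 patients will be included prospectively to compare treatment arms (115 patients for each"), under the assumptions "5% vs 15%; with power 0.8, alpha 0.05". The hazard ratio "for developing a grade 3-5 AE is 3.2 times higher among patients in the experimental treatment arm". Sidedness is not given, and this is the only significance level for the primary comparison.

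**Interim analyses {21b}.** The first look comes when safety data exist for 80 prospective patients, with the same Cox regression and endpoint as the primary analysis. Enrolment is discontinued "If the interim analysis shows a significant difference between the experimental arm and the control arm in terms of the primary endpoint" before the full sample is reached. If the trial continues, "as soon as safety data are available for 160 patients enrolled in the trial, a second interim analysis will be conducted", by the same approach. Both looks may also include 255 retrospective controls if similarity checks are passed.

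**Discussion.** The looks are there to stop enrolment early "in case the primary safety endpoint would be significantly more frequent in one of both arms".

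**Primary analysis {20a}.** The final comparison is a chi-square or Fisher test plus the Cox model, with no adjusted level.

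**Oversight {5d}{21a}.** A treatment monitoring group discusses the interim results and decides on continuation. It is given no threshold.

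**Dissemination plans {31a}.** "The results of the intermediate analysis can be used for abstracts or manuscripts, prior to the publication of the results of the primary analysis".

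**The concern.** The primary hypothesis can be declared significant on three occasions, and nothing separates the level used at an interim look from the level used at the end. Testing the same accumulating data three times at 0.05 gives more than a 5% chance of at least one false positive.

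The claim at stake is that the WHO all-oral regimen causes more severe adverse events than the Niger strategy. The Discussion says the findings will immediately inform national treatment, and interim results may be published ahead of the primary analysis. An unadjusted crossing at 80 or 160 patients could therefore become the public conclusion of the trial.

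**Working it through.** **1. Reproduce the plan's sample size.** Inputs from Sample size {14}: hazard ratio 3.2, power 0.80, alpha 0.05, 1:1 allocation, event rates 5% and 15% (mean 10%).

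- Schoenfeld, two-sided: events = (1.96 + 0.842)² / (0.25 × (ln 3.2)²) = 7.85 / (0.25 × 1.353) = 23.2. Patients = 23.2 / 0.10 = 232, within 1% of 230. With 23 events the power is 79.6%.
- Freedman, one-sided: 23 events, 230 patients.

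Both routes spend the full 0.05 on a single test, with no allowance for interim looks.

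**2. Error with three tests at two-sided 0.05.** Take information as proportional to patients: t = 80/230 = 0.348, 160/230 = 0.696, and 1. The three z-statistics are correlated as √(tᵢ/tⱼ): 0.707, 0.590 and 0.834. Integrating the trivariate normal with |z| > 1.96 at each look:

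| Up to look | Cumulative type I error |
|---|---|
| 80 patients | 5.0% |
| 160 patients | 8.3% |
| 230 patients | 10.6% |

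Half of the total, 5.3%, lies in the direction of harm from the WHO regimen. The nominal figure in that direction is 2.5%.

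**3. Sensitivity.**

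- Information fractions of 0.45/0.80 and 0.25/0.60 at the two looks: 9.9% and 11.3%.
- Null simulation with true event rates of 5% to 25%: 9.4% to 11.1% (log-rank) and 9.7% to 11.5% (chi-square).
- 255 retrospective controls pooled at the interims only, assuming they are exchangeable with the trial controls: about 11.5%.

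**4. The other reading: a crossing stops enrolment, and the claim rests on a later analysis of everyone already enrolled.** Assume uniform accrual of 230 patients over the 36 months in Trial status, or 6.4 per month. Safety data are complete 9 months (shortest treatment) to 17 months (11 months' treatment plus 6 months' grading) after enrolment. When the first 80 patients are complete, between 80 + 6.4 × 9 ≈ 138 and 80 + 6.4 × 17 ≈ 189 are enrolled. At the second look the range is 160 + 6.4 × 9 ≈ 218 up to all 230. Simulating with 140 to 185 and 217 to 230 gives an overall error of about 5.3% to 5.8%.

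**5. Limits that restore 5%, and their cost.** For looks at 80/160/230:

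| Rule | Nominal two-sided p | Overall error | Chance of crossing at 80 patients, 5% vs 15% |
|---|---|---|---|
| Unadjusted | 0.05, 0.05, 0.05 | 10.6% | 35% |
| O'Brien-Fleming type | 0.0007, 0.016, 0.045 | 5% | 0.5% |
| Haybittle-Peto | 0.001, 0.001, 0.05 | 5.05% | 1.2% (2.7% if \|z\| > 3 is used) |
| Pocock type | 0.022 at each look | 5% | 19% |

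The last column is an exact binomial calculation for the chi-square statistic with 40 patients per arm. Expected events at 80 patients are 40 × 0.05 + 40 × 0.15 = 8. Even an 8-to-0 split gives only z = 0.20 / √(0.1 × 0.9 × 2/40) = 2.98.

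Power of the final test alone with 23 events is Φ(ln 3.2 × √23 / 2 − c) = Φ(2.79 − c): 79.6% at c = 1.96, 78.2% at 2.01 and 69.3% at 2.285. Counting crossings at any look, power is about 79% for O'Brien-Fleming, 80% for Haybittle-Peto and 73% for Pocock.

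**The case against.** **Boundaries belong in an analysis plan that is not shown.** Numerical limits are often placed there. But this article does not leave the rule out: it gives the timing, test, trigger and consequence, and the trigger is unqualified significance. The monitoring group's role does not supply a limit either.

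**A reader might infer that the trial's error simply is 10.6%.** The document does not support that without conditions. No level is printed beside the interim rule, and sidedness is unstated; the two-sided reading rests on the chi-square test and on the Discussion allowing a difference in either direction. More importantly, crossing only ends enrolment. The dissemination text distinguishes interim results from the primary analysis, so a later analysis of everyone enrolled is a fair reading, and under it the inflation is slight. This part of the objection stands. The 10.6% also counts errors in both directions; the harm claim alone carries 5.3%.

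**Early stopping exaggerates the hazard ratio.** This is tempting as support for a strict limit, but it works the other way. With 8 events, just crossing 1.96 implies a hazard ratio of about exp(1.96 × 2/√8) = 4.0; just crossing 3.40 implies about 11. Stricter limits make early stops rarer but more exaggerated when they occur.

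**Strict limits defeat the purpose of the looks.** The Discussion justifies them by not exposing more patients than needed to a less safe regimen. O'Brien-Fleming or Haybittle-Peto limits nearly disable the first look. This stands as a cost to disclose.

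**Publication during enrolment.** A reader might infer that the plan intends it. The text permits release before the primary publication and is silent on whether enrolment must have ended.

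**Conclusion.** The point holds in conditional form. The stopping rule is stated with no level of its own, the sample size spends the full 0.05 on one test, and the plan does not say which analysis is conclusive after an early stop.

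If every look uses two-sided p < 0.05 and a crossing is taken as the conclusion, the overall error is about twice the stated 0.05. If only a later analysis of all enrolled patients carries the claim, the error stays close to 5%. The second figure assumes uniform accrual. The permission to publish interim results first makes the less favourable reading a real possibility. An unconditional statement that the error is doubled would go beyond the document; so would a statement that it is controlled.

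**What to change.** **Interim analyses {21b}.** State a group-sequential rule with overall two-sided alpha 0.05 for the comparison of randomised patients, with information fractions based on events. O'Brien-Fleming type (nominal p about 0.0007, 0.016, 0.045) or Haybittle-Peto (about 0.001, 0.001, 0.05) would do. If a usable first look is wanted, a Pocock-type level of about 0.022 at each look also controls the error. Treat any analysis that pools the retrospective cohort as supportive. State which analysis is conclusive after an early stop: the one at the crossing, or the later one of all enrolled patients.

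**Dissemination plans {31a}.** Release interim comparative results only once enrolment has stopped. Clinicians and patients are not blinded, so earlier release could affect the grading of events.

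**Cost.** Protocol wording only; no extra patients or data. O'Brien-Fleming and Haybittle-Peto leave final power almost unchanged, but cut the chance of stopping at 80 patients from about 35% to about 0.5% to 3% under 5% versus 15%. Pocock keeps that chance near 19%, but lowers the power of the final test from about 80% to 69%. Keeping pooled analyses supportive gives up the speed the retrospective cohort was meant to bring, and interim publication may be delayed. The choice and its cost should be stated openly, given the ethical reason for the looks.
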